## Does the study have ethical approval?

Yes (code: IR.IUMS.REC.1403.547)

## Research Questions & Hypotheses

*(All hypotheses are stated as null hypotheses.)*

### 1. PVR:

- $H_0$ : There is no significant difference in mean PVR before and after treatment in the real IFC group.
- $H_0$ : There is no significant difference in mean PVR after treatment between the real IFC and sham IFC groups.

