### **Problem Statement**

BOO is typically diagnosed via pressure-flow studies assessing urinary flow rate and detrusor pressure (2). In women, a bladder outlet obstruction index (BOOI) >18 indicates obstructive voiding dysfunction. Elevated PVR (>50 mL) and excessive daytime urinary frequency are key evaluable symptoms (8, 9). Patients often face challenges such as frequent bathroom visits, sleep disruption, and persistent daytime anxiety (10). Chronic or acute urinary retention (painful or painless) and urinary tract infections are additional complications (1).

Definitive diagnosis of voiding dysfunction relies on patient history and urodynamic testing (1). A 3-day voiding diary, uroflowmetry, ultrasound-determined PVR, pelvic floor electromyography (EMG) to differentiate structural from functional obstruction, and endoscopic evaluation are clinical diagnostic tools for voiding dysfunction (1, 11). PVR and bladder emptying efficiency are commonly used to assess treatment efficacy in voiding dysfunction, including BOO (12). Studies indicate that symptoms alone are unreliable for diagnosis of this dysfunction. Abnormal uroflowmetry and pressure-flow studies are essential to distinguish between impaired detrusor contractility and BOO. A maximum flow rate <15 mL/s and PVR >50 mL are reliable diagnostic markers for voiding dysfunction (9).

In voiding dysfunction, treatment aims to normalize voiding patterns and prevent complications. First-line therapies for functional voiding dysfunction include pelvic floor physiotherapy and biofeedback. Additional options (though lacking robust evidence) include psychological interventions, medications such as alpha-blockers, botulinum toxin injections, and GABA agonists (2). Intermittent catheterization (CIC) and electrical stimulation (invasive or noninvasive) are also employed (1).

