### **Statistical Analysis**

Descriptive information regarding the demographic characteristics of individuals in both groups will be given as means (standard deviations) for quantitative variables and as frequencies (percentages) for qualitative variables. For comparing of each demographic variable between the two study groups, the independent t-test for normally distributed quantitative variables and the Mann-Whitney test for non-normally distributed quantitative variables will be applied. The chi-square test will be conducted to compare qualitative variables.

The normality of the data in the study groups will be tested using the Shapiro-Wilk test. To comprehensively examine the extracted data, the following procedures will be carried out, as elaborated below.

To compare the mean of each variable in both groups before the intervention, two weeks after the intervention, and after a three-month follow-up period, the two-way repeated measures ANOVA will be employed, assuming the data are normally distributed. In the case of non-normality, a nonparametric equivalent will be used.

For the comparison of the mean of the variables between both groups at every time point (before the intervention, at two weeks after the intervention, and after a three-month follow-up), the two independent sample t-test will be used if the data is normally distributed and the Mann-Whitney test if the data is distributed non-normally.

To determine differences in the mean of the variables of both groups over the study period, the one-way repeated measures ANOVA will be used. In the presence of a statistically significant difference in the variable mean over time, the post hoc test with Bonferroni and Tukey corrections will be utilized. The data will be analyzed using SPSS version 26 software. The significance level in this study is assumed to be 5%.

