### **Solutions to Ethical Issues:**

1. Prior to intervention, all patients will receive a full explanation of group allocation and treatments. All patients will be assured that if any clinically significant improvement is demonstrated in either group, the effective treatment will be provided to the other group with the same duration and quality after study completion.
2. Participation is entirely voluntary. Written informed consent will be obtained from all patients before treatment initiation.
3. Principles of confidentiality and data protection will be strictly maintained.
4. All participants retain the right to withdraw from the study at any stage without consequences.

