### 2. Qmax:

- $H_0$ : There is no significant difference in mean Qmax before and after treatment in the real IFC group.
- $H_0$ : There is no significant difference in mean Qmax after treatment between the real IFC and sham IFC groups.

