### 3. 24-Hour Urinary Frequency:

- $H_0$ : There is no significant difference in mean 24-hour urinary frequency before and after treatment in the real IFC group.
- $H_0$ : There is no significant difference in mean 24-hour urinary frequency after treatment between the real IFC and sham IFC groups.

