### 4. LUTS Severity (ICIQ-FLUTS):

- $H_0$ : There is no significant difference in mean ICIQ-FLUTS scores before and after treatment in the real IFC group.
- $H_0$ : There is no significant difference in mean ICIQ-FLUTS scores after treatment between the real IFC and sham IFC groups.

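### For five outcomes the protocol sets a before-after null in the real IFC arm beside the real-versus-sham null and never labels it descriptive, although it can be rejected with no IFC effect

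*Protocol*

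**What the plan says.** Research Questions & Hypotheses gives items 1 to 5 two nulls each. The first bullet is a before-after null in the real IFC arm:
- PVR: "There is no significant difference in mean PVR before and after treatment in the real IFC group"
- Qmax: "There is no significant difference in mean Qmax before and after treatment in the real IFC group"
- 24-hour frequency: "There is no significant difference in mean 24-hour urinary frequency before and after treatment in the real IFC group"
- ICIQ-FLUTS: "There is no significant difference in mean ICIQ-FLUTS scores before and after treatment in the real IFC group"
- PFDI-20: same form.

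The second bullet is the randomised contrast, for PVR "There is no significant difference in mean PVR after treatment between the real IFC and sham IFC groups". Item 6 (PGIC) has only the between-arm null. No before-after null is written for the sham arm.

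Statistical Analysis plans, in this order, a two-way repeated-measures ANOVA on both groups, between-group tests at each time point, and a one-way repeated-measures ANOVA over time. After a significant result over time, "the post hoc test with Bonferroni and Tukey corrections will be utilized". The significance level is 5%.

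The Problem Statement gives both groups medication, urotherapy and voiding exercises. Section 3 (Interventions) sets ten urotherapy sessions for everyone, and Key Methodological Strengths describes the urotherapy as identical in the two groups.

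**The concern.** The stated aim, in Study Design, is to compare routine urotherapy alone with urotherapy plus IFC. Change from baseline in the real IFC arm mixes any IFC effect with the effects of medication, urotherapy and exercises, with placebo response, and with regression to the mean. The sham arm exists to remove these, and a one-arm test discards it.

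Regression to the mean is direct for two outcomes. The definition of obstructive voiding dysfunction lists Qmax and PVR among the diagnostic criteria, and the Problem Statement says "A maximum flow rate <15 mL/s and PVR >50 mL are reliable diagnostic markers for voiding dysfunction". Section 4 (Outcome Measures) makes both primary endpoints. Women enter partly because these values are abnormal, so a repeat measurement tends to be less abnormal without any treatment.

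Because the before-after statement is a formal null with its own test and no descriptive label, a rejection could be read as an answer to whether IFC works.

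**Working it through.** **Stated design figure.** Sample Size Calculation Method gives 14 per group at 95% confidence and 80% power, but no endpoint, difference or SD, so 14 cannot be reproduced. Solving backwards (two-sided, normal approximation), it corresponds to a standardised difference of √(2/14) × (1.960 + 0.842) = 1.06. Only n = 14 is used below.

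**Step 1: change shared by both arms, no IFC effect.** Let δ be the mean change common to both arms, in units of the SD of change. The documents give no value, so a range is assumed. A paired t-test stands in for the three-visit one-way ANOVA. It rejects when |t| on 13 df exceeds 2.160, with noncentrality δ√14.

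| δ (assumed) | δ√14 | Within-arm rejection | Between-arm rejection (simulated) |
|---|---|---|---|
| 0.3 | 1.12 | 18% | 5.0% |
| 0.5 | 1.87 | 41% | 5.0% |
| 0.8 | 2.99 | 79% | 4.9% |
| 1.0 | 3.74 | 93% | 5.0% |

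The between-arm rate does not move because δ cancels in the difference. To read the scale: if repeat values correlate 0.6 (assumed), the SD of change is √(2 × 0.4) = 0.894 outcome SD, so δ of 0.3 to 1.0 is a shift of 0.27 to 0.89 outcome SD. Some shared change is plausible on the protocol's own evidence. Its literature review reports a normalised flow pattern in 33% of children given urotherapy alone, though in a different population.

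**Step 2: selection alone, with no effect of any treatment.** This applies to Qmax and, with the direction reversed, to PVR. Take a standard normal measurement with retest correlation r and enrol only values below c. The expected change is (1 − r) × φ(c)/Φ(c). For r = 0.5 and c = −1 it is 0.5 × 1.525 = 0.76 SD. For r = 0.9 and c = 0.5 it is 0.1 × 0.509 = 0.05 SD. Simulated within-arm rejection at n = 14 (r and c are assumptions):

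| r | c = −1 | c = 0 | c = 0.5 |
|---|---|---|---|
| 0.5 | 83.7% | 32.6% | 15.5% |
| 0.7 | 58.5% | 20.5% | 11.1% |
| 0.9 | 22.4% | 9.4% | 6.9% |

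The between-arm test, on post-treatment values, rejected in 4.8% to 5.2% of trials throughout.

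**Step 3: reach of each argument.** Shared treatment covers all five outcomes. Selection is direct for Qmax and PVR. ICIQ-FLUTS, 24-hour frequency and PFDI-20 are not among the criteria listed in the definition of obstructive voiding dysfunction, so for them it is at most indirect.

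**The case against.** The strongest reply is that the randomised comparison is already there. Each of the five items has a valid between-arm null, and Statistical Analysis puts between-group methods before the one-way ANOVA. This stands, and it limits the point.

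A reader might infer that the before-after nulls lead the analysis and that the trial will declare IFC effective on them. The documents do not support that. The before-after null comes first only in bullet order, and no hierarchy is stated. A reader might also expect an argument from significance in real IFC and non-significance in sham. No passage announces it, and no sham before-after null is written. A statistical analysis plan that is not shown may say which test decides. The protocol itself, however, writes the before-after statements as hypotheses and assigns a test, so their role should be settled there.

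Three further readings go too far:
- That selection on abnormal values undermines all five outcomes equally. Enrolment is by the urologist's diagnosis, the screening section gives no numeric cut-off, and the direct link is to Qmax and PVR.
- That Tukey comparisons are invalid because the visits are repeated in the same women. They can hold for equally correlated repeated measures with the within-subject error term. The firm fault is naming two corrections without saying which governs.
- That the review should decide what triggers the treatment offer. It can only note that the wordings differ.

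The rejection rates rest on assumed inputs and a two-visit approximation. That limits their precision. The direction does not depend on them.

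**Conclusion.** The point holds in limited form. Five outcomes carry a formal before-after null in the real IFC arm that cannot isolate IFC and is not marked descriptive. With no IFC effect it is rejected in about 18% to 93% of trials for assumed shared changes of 0.3 to 1.0 SD of change at n = 14, against 5% for the between-arm test. For Qmax and PVR, selection alone gives about 7% to 84% over the assumed correlations and cut-offs. The valid comparison is present, so this should be corrected but does not undermine the design.

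Two wording matters go with it. The post hoc rule names two corrections. The trigger for the post-trial treatment offer is worded in three ways: Study Design refers to significant improvements at the end of the study. Solutions to Ethical Issues says "if any clinically significant improvement is demonstrated in either group, the effective treatment will be provided to the other group". Section 6 (Ethical Considerations) refers to significant benefits and offers active treatment to the sham group.

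**What to change.** - For items 1 to 5, make the real-versus-sham comparison, adjusted for the outcome's baseline value, the only efficacy hypothesis. The baselines are already collected. Adjustment is for precision and chance imbalance in small arms, since the unadjusted null is already valid.
- Set each hypothesis at the post-treatment assessment the protocol gives that outcome. Study Design puts the questionnaires at the final session and uroflowmetry two weeks after treatment, so one label should not be imposed on all.
- Leave PGIC as an unadjusted between-arm comparison, because it has no baseline.
- Report within-arm changes as means with 95% confidence intervals, labelled descriptive and not as evidence that IFC works.
- Name one post hoc correction for any visit contrasts kept.
- Reconcile the three statements of the treatment-offer trigger.

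The cost is protocol wording and a simpler analysis. No extra patients, visits or data are needed.

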### 2. Qmax:

- $H_0$ : There is no significant difference in mean Qmax before and after treatment in the real IFC group.
- $H_0$ : There is no significant difference in mean Qmax after treatment between the real IFC and sham IFC groups.

### 3. 24-Hour Urinary Frequency:

- $H_0$ : There is no significant difference in mean 24-hour urinary frequency before and after treatment in the real IFC group.
- $H_0$ : There is no significant difference in mean 24-hour urinary frequency after treatment between the real IFC and sham IFC groups.

### 4. LUTS Severity (ICIQ-FLUTS):

- $H_0$ : There is no significant difference in mean ICIQ-FLUTS scores before and after treatment in the real IFC group.
- $H_0$ : There is no significant difference in mean ICIQ-FLUTS scores after treatment between the real IFC and sham IFC groups.

### 5. Pelvic floor symptom severity (PFDI-20):

- $H_0$ : There is no significant difference in mean PFDI-20 scores before and after treatment in the real IFC group.
- $H_0$ : There is no significant difference in mean PFDI-20 scores after treatment between the real IFC and sham IFC groups.

### 6. Patient-Reported Improvement (PGIC):

- $H_0$ : There is no significant difference in mean PGIC scores after treatment between the real IFC and sham IFC groups.

## Definitions of Key Terms

### 1. Voiding Dysfunction

- **Conceptual Definition:** A set of symptoms experienced during or after urination, including: weak urinary stream, splitting/spraying of urine, intermittent flow, difficulty initiating voiding, straining to void, sensation of incomplete emptying, prolonged terminal dribbling, post-void dribbling, need for immediate re-voiding and urination only in specific positions (8, 21).
- **Operational Definition:** In this study, patients diagnosed with voiding dysfunction by a referring urologist will be enrolled.

### 2. Obstructive Voiding Dysfunction

- **Conceptual Definition:** Reduced urinary flow rate ( $Q_{max} < 15 \text{ mL/s}$ ) and elevated detrusor pressure ( $> 20 \text{ cm H}_2\text{O}$ ) during voiding in the absence of infection or overt pathology. It is diagnosed via pressure-flow study (PFS) and uroflowmetry and may be associated with increased post-void residual (PVR) (6, 8). The urodynamic characteristics in this dysfunction are as following:
  - Filling phase: Normal detrusor stability (no involuntary contractions).
  - Voiding phase: Electromyographic (EMG) activity in pelvic floor muscles; variable PVR (22).
  - Bladder Outlet Obstruction Index (BOOI): A value  $> 18$  supports diagnosis (12).
- **Operational Definition:** In this study, patients with functional obstructive voiding dysfunction will be diagnosed by a urologist. Diagnostic criteria: BOOI,  $Q_{max}$ , voiding time (urodynamic testing) and PVR (ultrasound).

### 3. Urinary Incontinence

- **Conceptual Definition (ICS Standards):** involuntary urine leakage which affects social life and quality of life of patient. It includes 3 categories:
  - Stress urinary incontinence (SUI): Leakage due to increased intra-abdominal pressure (e.g., coughing, sneezing) (23, 24)
  - Urge urinary incontinence (UII): Leakage preceded by urgency.
  - Mixed urinary incontinence (MUI): Combined SUI and UII symptoms (23).
- **Operational Definition:**  
Patients must answer "yes" to at least one screening question:

1. *"In the past month, have you experienced urine leakage after specific physical activity (e.g., lifting, laughing, coughing)?"*
2. *"In the past month, have you had sudden urges to urinate that were difficult to control?"* (25).

#### 4. Urotherapy

- **Conceptual Definition:**  
Non-surgical and non-pharmacological interventions to normalize urinary/defecation patterns and prevent functional disorders through repetitive training (26).
- **Operational Definition:**  
Standard urotherapy in this study includes:
  - Education on urinary tract function.
  - Fluid intake management.
  - Scheduled voiding (every 2–3 hours).
  - Proper toileting posture (spinal alignment, relaxed pelvic floor).
  - Instruction on intermittent catheterization (if needed).
  - Pelvic floor muscle training: 10-second contractions followed by 30-second relaxation.
  - High-fiber diet and regular bowel habits (1, 3).

#### 5. Interferential Current (IFC)

- **Conceptual Definition:**  
A low-frequency (1–100 Hz), amplitude-modulated current generated by interference of two medium-frequency (1–10 kHz) currents. It penetrates deep tissues by overcoming skin impedance (16, 18). It is Recommended to use this current for 20–30 minutes per session for non-acute conditions (19).
- **Operational Definition:**
  - Device: Standard electrotherapy unit (Novin, Iran).
  - Parameters:
    - Carrier frequency: 4,000 Hz
    - Beat frequency: 80–160 Hz
    - Duration: 20 minutes (pelvic region).

- Electrode placement: Cross-shaped over pubic symphysis and ischial tuberosities.
- Intervention protocol:
  - Real IFC group: Current intensity adjusted as high as possible according to patient tolerance.
  - Sham IFC group: Current applied for 1 minute in the first sensation of patient, then discontinued (27).

## Variables

### Severity of Lower Urinary Tract Symptoms (LUTS)

- **Conceptual Definition:**  
Subjective symptoms perceived by the patient, caregiver, or family, prompting medical consultation. These qualitative symptoms are typically identified during patient history-taking (23).
- **Operational Definition:**  
Assessed using the Persian version of the ICIQ-FLUTS questionnaire, which categorizes symptoms into:
  - Storage-phase symptoms
  - Voiding-phase symptoms (dependent variable)
  - Urinary incontinence symptoms (confounding variable).

### Post-Void Residual (PVR) Volume

- **Conceptual Definition:**  
The volume of urine remaining in the bladder after complete voiding without catheterization (10). PVR correlates with bladder capacity; higher pre-void volumes yield higher PVR (15). It should be performed  $\leq 60$  seconds post-void via ultrasound to minimize refilling artifacts (bladder refills at 1–14 mL/sec) (10). PVR  $> 50$  mL suggests voiding dysfunction (13).
- **Operational Definition:**  
it will be measured by pre- and post-void ultrasound performed by a urologist (13).

### Maximum Urinary Flow Rate (Qmax)

- **Conceptual Definition:**  
The peak flow rate (mL/sec) during voiding, denoted as Qmax (10). Qmax  $< 15$  mL/sec in women indicates voiding dysfunction (13).

- **Operational Definition:**  
Recorded during **uroflowmetry** by a urologist.

## Voiding Time

- **Conceptual Definition:**  
Total duration of urination, including interruptions. It matches flow time if voiding is continuous (10).
- **Operational Definition:**  
Extracted from **uroflowmetry** reports.

## Urinary Flow Pattern

- **Conceptual Definition:**  
The shape of the flow curve on uroflowmetry:
  - **Normal:** Bell-shaped, continuous.
  - **Abnormal:**
    - **Obstructive:** Flattened/prolonged.
    - **Detrusor-sphincter dyssynergia (DSD):** Intermittent/spiky (11, 23).
- **Operational Definition:**  
Obtained from **uroflowmetry** (pre- and post-treatment) by a urologist.

## Patient Global Impression of Change (PGIC)

- **Conceptual Definition:**  
A global assessment tool for any patient-reported changes (improvement or deterioration) post-treatment (28).
- **Operational Definition:**  
Evaluated using the PGI-C questionnaire post-intervention.

## Literature Review

### 1. Kajbafzadeh et al. (2015) (20)

#### Study Design:

Interventional study on 36 children (5-13 years) with underactive bladder (UAB), divided into two groups:

- **Group 1:** Standard urotherapy alone (n=18)
- **Group 2:** Standard urotherapy + interferential current (IFC) (n=18)

#### **Inclusion Criteria:**

- Urodynamically confirmed UAB
- Poor response to pharmacotherapy
- Intermittent urinary flow pattern, low flow rate (<15 mL/s), prolonged voiding time, voiding frequency <3/day, straining, PVR >20 mL

#### **Intervention:**

- **Standard urotherapy:** Education on urinary tract function, fluid intake, scheduled voiding (every 2–3 hours), proper toileting posture.
- **IFC:** 20-minute sessions (carrier frequency: 4,000 Hz) using cross-shaped electrode placement (pubic symphysis + ischial tuberosities).

#### **Outcomes:**

- **IFC group showed:**
  - Significant reduction in PVR ( $p<0.05$ )
  - Increased voiding frequency ( $p<0.05$ )
  - Improved Qmax and reduced voiding time ( $p<0.05$ )
  - 77% normalized urinary flow pattern vs. 33% in urotherapy-only group.

#### **Conclusion:**

IFC enhances bladder emptying in pediatric UAB by modulating neuromuscular function.

## **2. Sharifi-Rad et al. (2019) (14)**

#### **Study Design:**

Interventional study on 23 neurologically intact children with primary bladder neck dysfunction (PBNB).

#### **Inclusion Criteria:**

- Symptoms >6 months, poor drug response
- Abnormal uroflowmetry (flat curve, delayed EMG silence >6 sec, low Qmax)

#### **Intervention:**

- 15 IFC sessions (4,000 Hz, 20 min/session) + standard urotherapy.

#### **Results:**

- **Significant improvements in:**
  - Qmax ( $p<0.01$ )
  - PVR ( $p<0.01$ )
  - EMG silence latency ( $p<0.01$ )

#### **Conclusion:**

IFC mitigates functional bladder outlet obstruction in PBNB.

### **3. Ladi Seyedian et al. (2020) (29)**

#### **Study Design:**

Randomized trial on 34 children with non-neurogenic bowel-bladder dysfunction (BBD).

